**Figure 1 figure1:**
[figure not shown]
Design of the career crafting intervention.

### Step 6: Evaluation of the Results

#### Overview

Both the effectiveness as well as the implementation process of the career crafting intervention will be systematically evaluated. The effectiveness of the intervention program will be evaluated quantitatively, by analyzing the variables of interest. The implementation process of the intervention will be examined through a process evaluation, both quantitatively, by examining the answers to survey items, and qualitatively, by asking for experiences of participants after the coaching session on the phone and in an open-ended question at the end of the last survey.

#### Effectiveness and Outcomes

The effectiveness of the career crafting training intervention will be examined by comparing the intervention and control groups on the outcomes that were gathered in the pre- and posttests. The main outcome measures of this study were job crafting, career self-management behavior, and employability. Perceptions on job crafting regarding personal resources were measured (9 items) [39], and perceptions on job crafting to change work aspects were measured (10 items) [7]. Perceptions on career self-management behavior were measured [10] by examining general career behaviors, career planning, career self-exploration, environmental career exploration, networking, voluntary human capital and skill development, and positioning behavior (9 items). Perceived employability was measured by asking for physicians’ willingness and mental and physical ability to continue working in their current profession until the retirement age (3 items) [3]. Additional outcome measures were job satisfaction [40], career satisfaction [41], work-home interference [42], work ability [43], and performance [44]. Additionally, background information was gathered on age, gender, type of employment contract, hours worked according to the contract, organizational tenure, and functional tenure. Data from the pre- and posttests of individuals could be linked with unique codes that were generated by the program Qualtrics.

#### Participants

The sample size was calculated on the basis of 95% power to reject the null hypothesis with a 2-tailed significance level of 5%. Assigning equal numbers of participants to the intervention and control groups, and based on the effects of job crafting training interventions on job crafting behavior [45,46], a total of 120 physicians (60 in each group) were needed. We aimed for 150 participants, to allow for 20% dropout. We widely communicated the possibility of participating in this intervention study to physicians, as explained in step 5. However, we did not reach all physicians (ie, 685 physicians in the academic hospital and 225 physicians in the general hospital), as we were not invited into all the departments of the hospital to give a presentation about the training content. In the end, 141 physicians participated; 107 physicians (76%) were employed by the academic hospital and 34 physicians (24%) worked in the general hospital.

#### Data Analysis

Depending on the assumptions for outliers, normality, and sphericity, we are planning to conduct 2-way, repeated-measures multivariate analyses of variance in SPSS (version 25.0 (IBM Corp)), to assess the *time* × *group* interaction effects of the intervention on the main and additional outcome measures. Subsequently, if the tests for assumptions are not violated, we will perform repeated-measures analyses of variance to further examine the effects within the control and intervention groups.

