Figure 1 shows the procedure of this experiment. Participants in both the intervention and control groups received an email inviting them to complete the pretest. A total of 1 week after receiving the digital survey, which was sent through the program Qualtrics (version April 2020), physicians in the intervention group received a 4-hour training intervention. In total, 7-14 physicians were planned to attend each training session. After that, they worked on their self-set goals for the next 4 weeks. Then, a coaching conversation took place on the phone. A total of 3 weeks after the coaching conversation, which was 8 weeks after the pretest, physicians in both groups received a link to the posttest.

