Apart from the above strengths, this study has some limitations. First, contamination may occur when participants in the intervention group communicate with waitlist-control participants about the content of the training. However, the chances of contamination are small, since physicians are widely spread across the organization. Second, because we use a field experiment, our control is limited. This means that participants might not adhere to the instructions, might be unable to attend the assigned training, might not complete both surveys, or could drop out completely. We deal with these problems by (1) keeping track of participants that want to change groups and (2) sending two reminders by email to complete the survey and four reminders to work on the self-set goals after the training. A third limitation is that in order to minimize dropout, we did not include a long-term follow-up measurement. A second follow-up measurement could have revealed the extent to which findings can be generalized across longer time periods.

In conclusion, the systematic development of the intervention based on parts of the IM protocol has resulted in a 4-hour career crafting group training intervention to support physicians in developing proactive work and career behaviors. Subsequent analyses in a follow-up study can provide valuable insights to physicians, managers, and policy makers about the intervention’s effectiveness for physicians.

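### With one pretest and one posttest, the planned time × group test is an unadjusted change-score comparison; adjusting the posttest for the pretest would be more precise at no cost in data

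*Protocol article*

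**What the plan says.** The protocol article, Data Analysis, says "we are planning to conduct 2-way, repeated-measures multivariate analyses of variance in SPSS", to assess the time × group "interaction effects of the intervention on the main and additional outcome measures". Its follow-up step is that "we will perform repeated-measures analyses of variance to further examine the effects within the control and intervention groups". No covariate is named in either step.

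There are two measurement occasions. Effectiveness and Outcomes describes "comparing the intervention and control groups on the outcomes that were gathered in the pre- and posttests". Step 5: Implementation places the second survey at a point "which was 8 weeks after the pretest, physicians in both groups received a link to the posttest", and the Discussion confirms that there is no later follow-up. Step 5 also says that randomisation was done separately in the two hospitals.

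Participants gives a requirement of 120 (60 per group), a target of 150 to allow for 20% dropout, and 141 recruited. The Discussion expects that some participants will not complete both surveys. It responds with reminders and with "keeping track of participants that want to change groups".

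**The concern.** A repeated-measures time × group test suggests a longitudinal analysis. With two occasions it reduces to comparing mean change between groups. Subtracting the pretest assumes that a one-point pretest difference carries over as a full point at posttest. Whenever ρ is below 1, that over-corrects and leaves avoidable noise in the estimate.

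Two things are at stake. The first is precision, in a trial that recruited 141 against a target of 150. The second is completeness. The repeated-measures procedure needs both surveys from each participant and, in its multivariate form, every included outcome. Anyone without a full record is therefore dropped unless something is done beforehand.

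**Working it through.** **Inputs from the protocol article.** Power 95%, two-sided 5%, equal allocation, 60 per group, 20% dropout, 141 recruited (Participants); two occasions (Effectiveness and Outcomes; Step 5). **Not given, so assumed:** ρ, taken over a range; equal pretest and posttest SDs; and that the 120 refers to the change-score test.

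**1. The plan's own figure.** The article gives no effect size or SD, so 120 cannot be reproduced directly. Solving back by normal approximation:

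- d = (1.960 + 1.645) × √(2/60) = 0.658 (exact t: 0.664).
- The dropout step does reproduce: 120 / (1 − 0.20) = 150.
- The achieved sample falls short of 120: 141 × 0.80 = 112.8, or about 56.4 per group.

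**2. Identity of the tests.** In one simulated data set with two occasions, the mixed-ANOVA interaction gave F = 7.0688 and the squared t statistic on change scores was 7.0688. The multivariate version is the same comparison made on the vector of change scores.

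**3. Variance.** Per participant, with common SD σ:

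- change score: 2σ²(1 − ρ)
- pretest-adjusted posttest: σ²(1 − ρ²)
- ratio: (1 − ρ²) / [2(1 − ρ)] = (1 + ρ)/2

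**4. Power at 56.4 per group.** For the change score, d√(n/2) = 0.658 × √28.2 = 3.495, and Φ(3.495 − 1.960) = Φ(1.535) = 93.8%; the exact t calculation gives 93.7%. With adjustment, 3.495 is divided by √[(1+ρ)/2]:

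| ρ (assumed) | Variance ratio | Standardised difference | Power |
|---|---|---|---|
| 0.5 | 0.75 | 4.036 | 98.1% |
| 0.7 | 0.85 | 3.791 | 96.6% |
| 0.9 | 0.95 | 3.586 | 94.8% |

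Put as sample size, if the change-score test needs 120, the adjusted analysis needs 120 × 0.75 = 90, 120 × 0.85 = 102, or 120 × 0.95 = 114. These figures are per outcome; power of the joint multivariate test was not computed.

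**5. Bias.** Simulation with 141 participants, 4,000 replicates, ρ = 0.6 and a true effect of 0.4 SD (all but the 141 assumed):

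| Situation | Change score | Adjusted |
|---|---|---|
| No missing data | −0.002 | −0.002 |
| No missing data, chance pretest imbalance above 0.2 SD | −0.11 | about 0 |
| Dropout depends on pretest, same way in both groups | −0.002 | about 0 |
| Dropout depends on pretest, opposite ways by group | −0.17 | 0.00 |
| Dropout in one group depends on the unseen posttest | 0.07 | 0.11 |

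Without missing data, the simulated SD of the estimate was 0.150 for change scores and 0.134 with adjustment. The variance ratio is (0.134/0.150)² = 0.80, as the formula gives at ρ = 0.6.

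**The case against.** The strongest reply is that the planned interaction is a valid between-group test in a randomised trial, so all that is lost is some efficiency. That stands. The gain is small at the implied effect, ρ is unknown, and at ρ = 0.9 the variance saving is only 5%. The effect size is back-solved and its scale is not stated.

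A second reply is that a condensed article may leave missing-data and analysis-population rules to a plan that is not shown. That also stands. The article never says that only complete cases will be analysed, and imputation before the test is not excluded. What can be said is that deletion follows from the named procedure if nothing else is done.

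Three stronger readings are tempting, and the document supports none of them:

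- **That change scores are biased here.** With complete randomised data both estimators are unbiased. Dropout related to the pretest biases change scores only if the relation differs between groups, and nothing in the article shows such a pattern. If dropout depends on the unseen posttest, adjustment is no protection and was slightly worse in the simulation.
- **That people who change groups will be analysed in the group they moved to.** The Discussion says only that they are tracked, which is compatible with analysis as randomised.
- **That covariate adjustment alone keeps everyone in the analysis.** It also loses anyone without a posttest. Retention needs a mixed model or imputation, and analysis by assigned group is a separate rule.

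**Conclusion.** The point holds as one about the choice of test. For each outcome, the planned analysis is a change-score t test that leaves part of the pretest information unused. Adjustment lowers the variance by 25%, 15% or 5% at assumed ρ of 0.5, 0.7 or 0.9, given equal SDs. If the 120 was sized for the change-score test, power at about 113 completers rises from about 93.7% to between 94.8% and 98.1%. That can make up for the recruitment shortfall, except at the highest ρ, where it falls just short of 95%.

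The change-score identity and the variance ratio are firm. The power figures depend on the stated assumptions. Protection against chance pretest imbalance, and against pretest-related dropout that differs by group, is a further advantage, but neither problem is shown to be present. The change is worth making because it is nearly free; the planned test is not invalid.

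**What to change.** For each outcome, estimate the between-group difference in posttest score, adjusted for the pretest of the same scale and for hospital, which was the randomisation stratum. Analyse every participant in the assigned group.

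To keep people who missed a survey, use multiple imputation or a likelihood-based mixed model. In the mixed model, both surveys should enter as outcomes with a common pretest mean across groups; a model with pretest only as a covariate would still drop those without a posttest.

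Because outcome-by-outcome models give up the joint test, either keep a multivariate test across the main outcomes (job crafting, career self-management and employability) or state a multiplicity rule for them.

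No new data are needed. The Results section says that the primary analyses had been run and the results submitted in September 2020, so the cost is a reanalysis. It should be labelled as a change from the planned analysis and reported beside the planned time × group result.

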In order for employees to successfully navigate within this complex environment, they must proactively take control over their working life by creating a resourceful, healthy, and motivating environment for themselves [5]. This can be done through career crafting, which is a relatively new concept in the literature, and is defined as “individuals’ proactive behaviors aimed at optimizing career outcomes through improving person-career fit” [6]. Career crafting entails both choices and changes to the current work environment (ie, job crafting) as well as actions focused on longer-term career design (ie, career self-management) [6]. Job crafting refers to the self-initiated behaviors that employees take to shape, mold, and change their jobs [7-9]. For example, people can craft social resources such as support or they can optimize tasks or situations that are hindering. An example of job crafting is limiting tasks that drain energy, such as reducing the time spent on meetings by 15 minutes per meeting. Career self-management is defined as the extent to which employees proactively develop their careers as expressed by diverse career behaviors [10]. An example of career self-management is networking behavior, in which someone proactively approaches others who can be helpful in shaping their career. Career crafting entails the combination of both types of behaviors. For example, an employee may reduce energy-draining activities (ie, through job crafting) by communicating firmer boundaries in meetings (eg, “I have 30 minutes for this meeting; what are our highest priorities?”). The time thus gained is used to proactively network with someone from another organization (ie, career self-management), who is employed in a position that is of interest to the employee, to learn about how he or she managed to get that position.

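### The planned analysis gives no error-controlled between-arm conclusion for each of the three unranked main outcomes

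*Protocol article*

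**What the plan says.** Step 2 of the article sets three objectives: to raise job crafting, career self-management and employability. The Effectiveness and Outcomes section repeats them without an order: "The main outcome measures of this study were job crafting, career self-management behavior, and employability". Job crafting is measured with two instruments, of 9 and 10 items. Five additional outcomes follow: job satisfaction, career satisfaction, work-home interference, work ability and performance.

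The Participants section sizes the trial at 95% power and a two-tailed 5% level, "based on the effects of job crafting training interventions on job crafting behavior", with the result that "a total of 120 physicians (60 in each group) were needed". This is the only place where a significance level appears.

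The Data Analysis section then plans multivariate repeated-measures analyses of time × group "interaction effects of the intervention on the main and additional outcome measures". If the assumption checks are passed, repeated-measures ANOVAs follow, and their stated purpose is to look at effects within each of the two groups.

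**The concern.** Three objectives call for three between-arm answers. As written, the first stage gives a joint answer: some combination of outcomes differs between arms. The second stage looks within arms, and a change in one arm without a change in the other is not a comparison of the arms. The step between the stages depends on distributional checks, which have no bearing on the error rate.

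A reader who wants to know whether employability improved must therefore take a univariate result from somewhere, and the text does not say which one or at what level. The main and additional outcomes go through the same analysis. What is at stake is that one significant scale among several could be presented as evidence that the training works, at a false-positive rate well above the 5% used to size the trial.

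**Working it through.** **The plan's own figures.** Allowing for dropout, 120 / (1 − 0.20) = 150, which reproduces the recruitment target. The 120 cannot be checked, because no effect size or SD is given. Solving backwards for 60 per arm, two-sided 5%, 95% power and a two-sample t test (my assumption):

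- Normal approximation: d = (1.960 + 1.645) × √(2/60) = 0.658.
- Noncentral t: d = 0.664.

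**Inputs.** Three main outcomes, or four scales if the job-crafting instruments are kept apart (Effectiveness and Outcomes); 60 per arm and 5% two-sided (Participants). The correlation between outcomes is not stated, so I assume equal correlations from 0 to 0.7.

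**Outcomes read one by one, no true effects.** With independent outcomes:

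- Either direction, 1 − 0.95^k: 1 − 0.95³ = 14.3%; 1 − 0.95⁴ = 18.5%.
- Benefit direction only, 1 − 0.975^k: 7.3% and 9.6%.

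With correlated outcomes, by multivariate-normal simulation:

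| Correlation | 3 outcomes, any direction | 4 scales, any direction | 3 outcomes, benefit | 4 scales, benefit |
|---|---|---|---|---|
| 0 | 14.3% | 18.5% | 7.3% | 9.6% |
| 0.3 | 13.7% | 17.4% | 6.8% | 8.7% |
| 0.5 | 12.5% | 15.6% | 6.3% | 7.8% |
| 0.7 | 10.9% | 13.0% | 5.4% | 6.5% |

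A single two-sided 5% test allows 5% in either direction and 2.5% in the benefit direction.

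**Multivariate test used as a gate.** With two time points, the time × group MANOVA is equivalent to Hotelling's T² on change scores. I simulated it at 60 per arm, with between-arm t tests at 5% after a significant T².

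- No true effects: the chance of any false significant outcome is about 4-5%, so a gate would work here.
- One outcome truly affected (d = 0.664): the chance of a false significant result on another main outcome is 8.6% to 9.6% for three outcomes (correlation 0.7 to 0). For four scales it is about 12-14% at correlations from 0 to 0.5 and about 11% at 0.7.
- Both job-crafting scales truly affected, four scales (correlation 0 to 0.5): about 9-10% on the other two.

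The multivariate test has by then been passed with probability above 80% (above 98% where both scales move), so the remaining true nulls are each tested at close to a full 5%.

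**Holm instead.** In the setting with three outcomes and one true effect, the false-positive rate on the other outcomes is 4.0% to 4.8%. For job crafting at the strictest step, alpha = 0.05/3 = 0.0167. The normal approximation gives Φ(3.605 − 2.394) = 88.7% power, and the noncentral t gives 88.4%.

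**The case against.** The strongest reply is that the planned between-arm test is multivariate, so it controls the error for the joint question. The 5% level appears only in the sample-size calculation, and nowhere does the article say that outcomes will be tested separately without adjustment. A reader might infer that each is tested at an unadjusted 5%; the text does not support that as a statement of fact. The figures above are therefore conditional on outcomes being read singly, or on the multivariate test being used as a gate.

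Three further readings go too far.

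- The 11-19% might be taken as the chance of a false claim of benefit. It counts rejections in either direction; the benefit figure is about half.
- The larger figures that come from counting all nine scales treat the additional outcomes as routes to success. The article separates them from the main outcomes and never says that one of them alone would establish effectiveness.
- The Introduction says "Career crafting entails the combination of both types of behaviors", from which one might require both components to be significant before any claim about career crafting. The objectives are three separate ones, and no composite criterion is set.

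It is also fair to say that multiplicity rules often sit in an analysis plan, which is not shown here, so the absence of an adjustment is not itself a finding. What remains is what the article does fix: unranked main outcomes, a second stage aimed within arms, and a condition for reaching it that does not control error.

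**Conclusion.** The point holds as one about the inferential sequence. Followed as written, the analysis does not answer each of the three objectives with a between-arm test at a controlled error rate. Read singly, the main outcomes carry about an 11-14% chance (three) or 13-19% chance (four scales) of a false significant result. A gate would leave about 9-10% or 11-14% once one outcome truly moves.

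These sizes rest on assumed equal correlations of 0 to 0.7. The gated and power figures also rest on an effect of about 0.66, back-solved from 60 per arm. Confidence in the structural point is high, and in the exact figures moderate. This is a cheap and worthwhile improvement; it does not invalidate the design.

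**What to change.** In Data Analysis, state that conclusions rest on the between-arm (time × group) test of each of the three main outcomes, with Holm adjustment over the three tests at a two-sided familywise 5%. Score job crafting as one average of its two standardised scales. Fixing the family at three matches the number of main outcomes that the article names, and avoids choosing between three and four tests after the data were seen. Report the five additional outcomes as exploratory, with confidence intervals and no claim of effect. The within-group ANOVAs can stay as description. If an analysis plan already contains such a rule, the article should state it.

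Holm needs no ranking of outcomes, so it can still be applied although data collection ended in March 2020. The change takes two or three sentences and no new data. There are two costs. Power for job crafting at the strictest step falls from the stated 95% to about 88% at 60 per arm, and an effect confined to one job-crafting scale would be diluted in the average.

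### The only outcome-level follow-up stated is a pre-post test within each arm, which does not estimate the intervention effect on any of the three main outcomes

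*Protocol article*

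**What the plan says.** Three statements in the protocol article matter here.

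- **Aim** (Effectiveness and Outcomes): "The effectiveness of the career crafting training intervention will be examined by comparing the intervention and control groups" on pretest and posttest outcomes. The same section says: "The main outcome measures of this study were job crafting, career self-management behavior, and employability". Step 2 sets these as three separate program objectives.
- **First analysis** (Data Analysis): repeated-measures multivariate analyses of variance, "to assess the *time* × *group* interaction effects of the intervention on the main and additional outcome measures". This step is introduced with "Depending on the assumptions for outliers, normality, and sphericity".
- **Follow-up** (Data Analysis): "Subsequently, if the tests for assumptions are not violated", then "we will perform repeated-measures analyses of variance to further examine the effects within the control and intervention groups".

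The stated condition for the follow-up is the assumption tests. A significant time × group interaction is not named as a condition. No between-group follow-up for individual outcomes is stated.

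**The concern.** The aim is a contrast between arms, but the outcome-level step is a test of change inside each arm. A change in one arm does not estimate the effect of the training, because the passage of time, answering the same survey twice and regression to the mean can move both arms. Nor is a significant change in one arm alongside a non-significant change in the other evidence that the arms differ: two arms with the same true change can easily fall on opposite sides of the 5% threshold.

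The multivariate interaction does not fill this gap. It pools several outcomes and does not say which one responded or by how much. A reader who wants to know whether job crafting, career self-management or employability improved because of the training is left, on the stated text, with the within-arm tests.

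The condition attached to the analysis is also poorly chosen. Sphericity concerns the equality of variances of differences between pairs of time points. With one pretest and one posttest there is only one such difference, so nothing can be violated.

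**Working it through.** **The plan's own figure.** Participants gives 120 physicians needed (60 per arm) and 20% dropout: 120 / (1 − 0.20) = 150, which matches the stated target. The 120 itself cannot be checked, because no effect size or SD is given. By the normal approximation, 60 per arm at 95% power and two-sided 5% corresponds to a standardised difference of (1.960 + 1.645) × √(2/60) = 0.66.

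**Inputs for the check.**
- 60 per arm and two-sided 5%: Participants.
- Two time points: pretest and posttest, Step 5.
- Assumed, not in the documents: the same true mean change in both arms, written dz and expressed in SDs of the individual change scores. The true group difference is therefore zero. A range of dz is shown.

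**Formula.** With two time points, a repeated-measures ANOVA in one arm is the square of a paired t test. Let p be the probability that this test is significant in either direction, and U the probability that it is significant in the direction of improvement (noncentral t, 59 df, noncentrality dz × √60). The arms are independent, so

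P(intervention improves significantly, control not significant) = U × (1 − p).

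Examples: at dz = 0, 0.025 × 0.95 = 0.024. At dz = 0.2, U ≈ p = 0.332, so 0.332 × 0.668 = 0.222.

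The last column is the rejection rate of the per-outcome time × group test in 100,000 simulated trials.

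| Common change dz | Within-arm power p | Intervention significant, control not | Time × group test rejects |
|---|---|---|---|
| 0 | 5.0% | 2.4% | 4.9% |
| 0.1 | 11.9% | 10.2% | not simulated |
| 0.2 | 33.2% | 22.2% | 5.0% |
| 0.25 | 48.9% | 25.0% | 5.1% |
| 0.3 | 62.8% | 23.4% | 4.9% |
| 0.4 | 86.2% | 11.9% | 5.0% |
| 0.5 | 96.8% | 3.1% | not simulated |

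(The row marked 0.25 was run at 0.2535.) The peak follows from p(1 − p), which cannot exceed 0.5 × 0.5 = 25%. The interaction column counts both directions; by symmetry about half of it, 2.5%, favours the intervention.

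**Other sample sizes.** The 141 enrolled give about 70 per arm, and 141 × 0.80 / 2 ≈ 56 after 20% dropout. At dz about 0.25 the probability is 24.7% with 70 per arm and 24.9% with 56. At dz = 0.5 it is 1.5% and 4.1%.

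**Overlap with the interaction test.** At dz from 0.2 to 0.3, about 90% of the misleading patterns occur without a significant time × group result for that outcome. The pattern and a significant interaction occur together in 2.3% to 2.5% of trials.

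**The case against.** The strongest reply is that the effectiveness test is already between-group. The time × group interaction matches the stated aim, and the within-arm step comes afterwards, as further examination. Nowhere does the article say that effectiveness will be judged from one arm being significant and the other not. This stands. A reader might infer that the whole analysis is within-group, or that the trial's false-positive rate is 20% to 25%; the article supports neither. The inflated figures apply only if conclusions are drawn from the within-arm pattern.

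It can also be said that reading the follow-up only after a significant interaction brings the joint chance down to about 2.4% per outcome, and that such gating may be left to a fuller plan. The first part is right for a per-outcome interaction. The planned test is multivariate, however: a real effect on one outcome could make it significant and leave the within-arm patterns of the others unprotected. Even with the gate, a within-arm test does not estimate the intervention effect. The point rests on the method that is stated, not on missing detail.

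A third reply is that nobody knows whether untrained physicians shift between two surveys 8 weeks apart. That is fair, and it is why the full range is shown rather than the values near the peak.

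Finally, a reader might infer that normality tests on short scales would readily fail and cancel the outcome-level analysis. The article does not support this: it gives no response format, only the employability measure has as few as 3 items, and no rejection rate can be computed. Nor does its silence show that no between-group estimate will ever be produced.

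**Conclusion.** The point holds in a limited form. The primary multivariate interaction is sound. The outcome-level follow-up, as stated, answers a different question from the one the article sets out to answer, and nothing in the text ties it to a significant interaction.

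If conclusions were taken from the within-arm pattern, the chance per outcome of an apparent effect with no group difference would lie between about 2% and 25%, depending on a common change that the documents do not give. It exceeds the 5% of the interaction test through the middle of the range and falls below it at both ends (0 and 0.5 SD). These figures assume normal change scores, equal true change and equal arm sizes.

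Separately, the sphericity condition is empty with two time points. Making the outcome-level analysis depend on assumption tests is a poor rule, but how often it would matter cannot be determined from the article.

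**What to change.** In Data Analysis, replace the within-arm follow-up by a between-group analysis of each outcome: the baseline-adjusted difference at posttest, or the univariate time × group interaction, with a 95% confidence interval. State that each outcome's conclusion rests on this contrast. Show pre-post change within each arm descriptively, without significance claims. Drop the sphericity condition, and do not let the per-outcome between-group analysis depend on passing assumption tests.

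No new data or software are needed. Because the Results section reports that evaluation began in April 2020 and results were submitted in September 2020, the cost is a small re-analysis or, if these contrasts already exist, a change in what is reported and how it is worded.
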